#### Intervention outcomes

Intervention outcomes are evaluated quantitatively and include effectiveness, safety and costs. Effectiveness is assessed across all study phases to provide internal benchmarks during implementation and to generate real-world effectiveness data. Effectiveness outcomes include the total number of excised LNs per SLNB procedure, including number of SLNs and non-SLNs; per-case SLN detection rate, defined as the proportion of SLNB procedures in which≥ 1 SLN is identified by the assigned tracer; per-node SLN detection by tracer, reported separately for ICG and ^99m^Tc-nanocolloid; detection time from axillary skin incision to excision of the first SLN; total SLNB procedure duration and pathological outcomes of excised SLNs, reported per-node and per patient and stratified by tracer and study phase. For Phase II in which both tracers are used concurrently, tracer concordance of SLNs is additionally assessed as a measure of agreement between tracers, and a within-patient comparison of per-case SLN detection is performed.

Safety is evaluated by systematic documentation of (serious) adverse events potentially related to ICG use during SLNB.

Costs are evaluated through a per-patient direct in-hospital cost analysis comparing ICG-guided and ^99m^Tc-nanocolloid-guided SLNB, based on hospital data and national costing guidelines. In addition, a 5-year budget impact analysis (BIA) models the financial implications of phased nationwide implementation of ICG-guided SLNB from a healthcare provider perspective. Patient-level cost data, including travel, sick leave and childcare needs, will be collected via patient questionnaires during Phases I and III and may inform future societal cost evaluations.

#### Patient-reported experience

Patient satisfaction is assessed using phase-specific postoperative questionnaires evaluating patient experience with ^99m^Tc-nanocolloid, ICG or both. As existing Dutch instruments (eg, Consumer Quality Index Mammacare) are insufficiently specific to capture experiences related to tracer use for SLNB, a context-specific questionnaire was co-developed with the patient panel (see Patient and public involvement) and patient-reported experience measure (PREM) experts.^59^ The questionnaire was iteratively refined based on PREM expert and patient panel feedback and pilot-tested to ensure clarity, relevance and content validity.

### Data collection

Baseline characteristics will be recorded for both patients and healthcare providers. Patient characteristics comprise demographic and clinical variables extracted from electronic medical records. Provider characteristics include year of birth, hospital affiliation, years of surgical experience, years of experience with SLNB for breast cancer, monthly SLNB volume and prior experience with ICG-fluorescence imaging.

Implementation outcomes will be captured through intraoperative case report forms, hospital administrative records and healthcare-provider questionnaires (table 1). Intervention outcomes will be obtained intraoperatively, from electronic medical records and from hospital financial records. Patient-reported experience and patient-level cost data will be collected using phase-specific postoperative patient questionnaires.

### Sample size

A formal sample size calculation was not performed, as the INFINITE trial primarily aims to implement ICG-guided SLNB in routine clinical practice, while concurrently collecting real-world data on effectiveness. Moreover, sample size estimation for stepped-wedge cluster designs is inherently challenging due to the sequential rollout across clusters.^41^ Instead, the study uses a convenience sample of real-world data from seven purposefully selected hospitals.

The seven participating hospitals collectively perform approximately 1500 SLNBs via axillary incision annually. Over the planned study period, this corresponds to approximately 2250 SLNB procedures. Given the limited exclusion criteria and an anticipated exclusion rate of ≤10%, approximately 2025 patients are expected to be eligible. Based on practical feasibility and consent rates observed during the early study phase, approximately 850 patients are expected to be included. The estimate is informed by initial inclusion patterns and may vary modestly over time as site-specific workflow stabilises.

The anticipated sample size is considered sufficient to estimate key quantitative outcomes with acceptable precision. For the primary implementation outcome, penetration, an expected Phase III sample of approximately 280 SLNB procedures yields a 95% CI of roughly ±6 percentage points when the proportion is near 50%, with narrower intervals for lower or higher values, based on binomial approximation. For effectiveness outcomes, assuming a per-case SLN detection rate of approximately 95% in Phase III, the corresponding 95% CI would be approximately ±2–3 percentage points. This level of precision is appropriate for pragmatic hybrid effectiveness-implementation research, in which the aim is to describe real-world uptake and contextual variation rather than to formally test hypotheses.

### Statistical analysis

#### Quantitative analysis

Baseline characteristics and quantitative outcome variables will be summarised using descriptive statistics. Continuous variables will be reported as means with SD or as median with IQR, based on distribution. Distributional assumptions will be assessed by visual inspection of histograms, and homogeneity of variances will be evaluated using Levene’s test. Dichotomous and categorical data will be presented as frequencies with percentages.

Where applicable, comparisons will be performed using the Student’s t-test for normally distributed continuous variables, the Mann-Whitney U-test for non-normally distributed continuous variables, and the χ^2^ or Fisher’s exact test for categorical variables.

Penetration, the primary implementation outcome, will be reported as a proportion with corresponding 95% CIs, without formal between-group comparisons. Adoption and fidelity outcomes will be reported descriptively as proportions with accompanying counts. Safety outcomes will be reported descriptively as proportions of patients experiencing ICG-related (serious) adverse events, with corresponding 95% CIs.

Effectiveness outcomes will be analysed according to study phase. A pre–post implementation analysis will compare observational cohorts of Phase I (^99m^Tc-nanocolloid) and Phase III (ICG). For these phases, effectiveness outcomes will be reported with 95% CIs and include per-case SLN detection rates, per-node SLN detection by tracer, number of excised LNs per procedure, detection time, SLNB duration and pathological outcomes of excised SLNs. Phase II will be analysed separately using a within-patient approach. In this phase, per-node SLN detection will be reported separately for ICG and ^99m^Tc-nanocolloid, and tracer concordance will be evaluated by quantifying agreement at the LN level. In addition, a paired within-patient comparison of per-case SLN identification by ICG versus ^99m^Tc-nanocolloid will be performed. Phase II outcomes will be reported descriptively with corresponding 95% CIs, using paired statistical methods where appropriate.

A cost overview analysis will be conducted from the healthcare provider perspective, comparing per-patient in-hospital costs for SLNB using ICG versus ^99m^Tc-nanocolloid. Total per-patient costs will be calculated by multiplying unit costs by expected resource use and summing all cost components. In addition, a 5-year BIA will be performed to model the economic impact of phased nationwide implementation of ICG-guided SLNB. Sensitivity analyses will be conducted by varying key parameters, including NIRF imaging system costs and annual surgical volumes. Patient-incurred costs will be summarised descriptively by converting patient-reported data on travel, sick leave and childcare into monetary values using national unit-cost references.

All quantitative analyses will be conducted using IBM SPSS Statistics (V.26) or R (V.4.4.0). All statistical tests will be two-sided, and a p-value of <0.05 will be considered statistically significant.

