### Study design and setting

#### Study design

The INFINITE trial is a multicentre, hybrid effectiveness-implementation study employing a stepped-wedge cluster design.^41^ The hybrid design enables concurrent evaluation of implementation outcomes, intervention outcomes and patient-reported experience, while the stepped-wedge design facilitates phased adoption of ICG-guided SLNB across participating hospitals. Quantitative analyses are complemented by an embedded mixed-methods component to capture contextual and process-related factors relevant to implementation.

Clusters implement ICG-guided SLNB across three sequential phases (figure 1). Phase I (pre-implementation period) is an observational cohort study reflecting current practice in which SLNB is performed using ^99m^Tc-nanocolloid as per standard of care. Phase II (transition period) is a fixed 6-month period in which SLNB is guided primarily by ICG, with concurrent use of ^99m^Tc-nanocolloid as a within-patient control to support a safe transition. Phase III (post-implementation period) is an observational cohort study representing the new practice, with SLNB performed using ICG as a single tracer.

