#### Timeline and cluster transition

All participating hospitals commenced Phase I on 18 April 2025. The trial spans 18 months and is divided into six consecutive 3-month periods. Three clusters, each comprising two or three hospitals, transition sequentially from Phase I to Phase II at 3-month intervals.

Cluster transitions are not randomised but scheduled pragmatically based on site readiness, defined as the availability of ICG, access to a NIRF imaging system and completion of training. Although non-randomised transitions may reduce control over potential time-related confounding, the relatively short study duration and stable clinical context minimise the likelihood of major secular trends, making this approach appropriate for a pragmatic implementation study.

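### The Phase I versus Phase III effectiveness comparison names only pooled independent-sample tests, although the staggered schedule gives the two cohorts different hospital mixes

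*Protocol article*

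**What the plan says.** The schedule is given in Study design and in Timeline and cluster transition. The roll-out is staggered: "Three clusters, each comprising two or three hospitals, transition sequentially from Phase I to Phase II at 3-month intervals". The starting point is common to every site: "All participating hospitals commenced Phase I on 18 April 2025". The middle phase has a set length: "Phase II (transition period) is a fixed 6-month period in which SLNB is guided primarily by ICG". The overall length is set as well: "The trial spans 18 months and is divided into six consecutive 3-month periods". The Figure 1 caption puts two hospitals in cluster 1, three in cluster 2 and two in cluster 3. The order of transition follows site readiness and is not randomised.

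Under Quantitative analysis, a pre–post analysis compares the Phase I and Phase III cohorts on detection per case and per node, nodes excised, detection time, procedure duration and pathology, with 95% CIs. The unpaired methods listed are Student's "t-test for normally distributed continuous variables, the Mann-Whitney U-test for non-normally distributed continuous variables" and chi-square or Fisher tests. The section adds: "All statistical tests will be two-sided, and a p-value of <0.05 will be considered statistically significant". Paired methods are named for Phase II only. No stratification, hospital term or covariate is mentioned for the pre–post contrast.

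The non-random transition is acknowledged in the strengths-and-limitations box, in Timeline and cluster transition and in the Discussion, but only as a source of time-related confounding or learning effects.

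**The concern.** In a staggered roll-out with a common start and end, early-moving hospitals spend little time in the first phase and much in the last; late-moving hospitals do the opposite. A pooled comparison of first and last phase is therefore partly a comparison of late-moving with early-moving hospitals. The argument offered against time trends (short duration, stable clinical context) does not touch this, because it arises even when nothing changes over time.

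Procedure time, node yield and detection may plausibly vary between hospitals, which were chosen for diversity in region, type and scale. A difference between the early and late clusters would be read in part as a difference between tracers, or would mask a real one. The phase contrast supplies real-world effectiveness evidence meant to inform guideline consideration, so the point estimates and intervals matter as well as the p-values.

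**Working it through.** **Inputs from the protocol article.** 18 months; 3-month steps; Phase II of 6 months; 2, 3 and 2 hospitals per cluster; about 850 inclusions; about 280 Phase III procedures (Sample size).

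**Assumptions, not in the article.** Equal and constant inclusion per hospital; a range of intraclass correlations (ICC).

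**Step 1: months per phase.** If the first transition were at month 6, cluster 3 would move at month 12 and finish Phase II at month 18, with no Phase III. If it were at month 0, cluster 1 would have no Phase I. The first transition is therefore at month 3.

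| Cluster (hospitals) | Phase I months | Phase II months | Phase III months |
|---|---|---|---|
| 1 (2) | 3 | 6 | 9 |
| 2 (3) | 6 | 6 | 6 |
| 3 (2) | 9 | 6 | 3 |

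Hospital-months in Phase I: 2×3 + 3×6 + 2×9 = 42. Phases II and III also total 42 each.

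**Step 2: the plan's own figures.** Phase III inclusions = 850 × 42/126 = 283, against the stated 280. With n = 280, the 95% half-width is 1.96 × √(0.25/280) = 5.9 points at 50% and 1.96 × √(0.95×0.05/280) = 2.6 points at 95%. These agree with the stated ±6 and ±2–3, so the schedule has been read correctly.

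**Step 3: cluster shares.**
- Phase I: 6/42, 18/42, 18/42 = 14.3%, 42.9%, 42.9%.
- Phase III: 18/42, 18/42, 6/42 = 42.9%, 42.9%, 14.3%.

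Unequal volumes change the percentages, not the direction. With cluster volumes v1 and v3, the ratio of cluster 1 to cluster 3 patients goes from 3v1 : 9v3 to 9v1 : 3v3, a ninefold shift whatever the volumes.

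**Step 4: bias in the pooled contrast.** Bias = (18/42 − 6/42) × (cluster 1 mean − cluster 3 mean) = 2/7 of that difference. For illustration, gaps of 2, 5 and 10 minutes give 0.6, 1.4 and 2.9 minutes; gaps of 2, 5 and 10 detection points give 0.6, 1.4 and 2.9 points.

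**Step 5: type I error of the pooled test.** Each hospital's share shifts by 1/7 (cluster 1), 0 (cluster 2) or −1/7 (cluster 3), so the sum of squared shifts is 4/49. With total variance 1 and 280 patients per phase:
- variance assumed by the test: 2/280 = 0.00714
- actual variance: (1 − ICC) × 2/280 + (4/49) × ICC
- type I error: 2 × [1 − Φ(1.96 × √(assumed/actual))]

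| ICC | Actual variance | Type I error |
|---|---|---|
| 0 | 0.00714 | 5.0% |
| 0.01 | 0.00789 | 6.2% |
| 0.02 | 0.00863 | 7.5% |
| 0.05 | 0.01087 | 11.2% |

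Simulation with 10,000 replicates gave 7.5% at ICC 0.02 and 11.2% at 0.05. With hospital fixed effects it gave 4.5% to 5.1% for ICCs from 0 to 0.20.

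**Step 6: cost of comparing within hospital.** At 280 per phase, each hospital contributes 20 and 60 patients (clusters 1 and 3, in either order) or 40 and 40 (cluster 2). Information = Σ n1n3/(n1 + n3) = 4×15 + 3×20 = 120, against 280×280/560 = 140 pooled. The SE ratio is √(140/120) = 1.08.

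**Step 7: what a hospital term cannot do.** The last Phase I data (cluster 3) end at month 9, and the first Phase III data (cluster 1) start at month 9. The phases share no calendar period. A model with hospital, period and phase effects on Phases I and III alone has rank 12 for 13 columns, so the phase effect is not identifiable once period is included.

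**The case against.** Several objections have force.

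- **Scope.** Penetration is reported as a single proportion with no between-group comparison, and Phase II compares the tracers within patients. Neither depends on hospital mix. A reader might infer that the trial's evidence on tracer performance is undermined as a whole. The article does not support that, although the Phase II pairing does not cover times or node yield.
- **Size.** A reader might infer that hospital differences as such are reported as tracer effects. Only two-sevenths of one particular difference is, and nothing shows that early and late clusters differ: readiness means ICG supply, imaging access and training, and diversity among seven hospitals is not a difference between clusters 1 and 3.
- **ICC.** The formula gives 17% at ICC 0.10 and 26% at 0.20. Near the article's 95% detection rate these imply between-hospital SDs of √(0.10×0.0475) = 6.9 and √(0.20×0.0475) = 9.7 points, which is unlikely so close to the ceiling. At ICC 0.01 the SD is 2.2 points. The half-width for a phase difference at 95% is already 1.96 × √(2×0.0475/280) = 3.6 points.
- **Wording.** The tests are introduced conditionally and not tied by name to the pre–post analysis, and covariate lists are normally left to an analysis plan. It would be wrong to say that the collected variables are excluded; the article is silent. Yet these are the only unpaired methods it states, and it does specify paired methods where it wants them.
- **Significance threshold.** The Sample size section says "the aim is to describe real-world uptake and contextual variation rather than to formally test hypotheses". A reader might see a contradiction with the 0.05 rule. The first remark justifies precision and the second is a general convention; dropping the threshold is a matter of preference. Nor does the descriptive aim answer the concern, since estimates and CIs carry the same bias.

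**Conclusion.** The point holds for the secondary effectiveness outcomes compared between Phases I and III. The imbalance in hospital mix follows from the stated schedule; the 14% and 43% shares rest on equal inclusion per hospital. Under that assumption the pooled contrast carries two-sevenths of any cluster 1 versus cluster 3 difference, which may be zero. Type I error is about 6% at an assumed ICC of 0.01 and 11% at 0.05; larger ICCs are illustrative and unlikely for detection rate. Nodes within a patient are also not independent, though the size of that effect has not been calculated. This should be fixed before Phase III results are known, but it does not threaten the primary result.

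**What to change.** Make the Phase I versus Phase III contrast within hospital:

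- for binary outcomes, a Mantel-Haenszel risk difference stratified by hospital;
- for node yield and times, regression with hospital fixed effects;
- for node-level outcomes, standard errors clustered by patient.

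Report adjusted differences with 95% CIs. Add hospital mix to the limitations. State there that the adjusted difference still cannot separate tracer from calendar time, because Phases I and III do not overlap; otherwise a reader might take the hospital-adjusted figure as a clean tracer effect.

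The cost is a change of wording and a regression or stratified estimate in place of a two-sample test. No new data are needed, since each patient's hospital is known. If hospitals do not differ, the SE is about 8% larger (variance about 17% larger).

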#### Phase II (transition period)

During the transition period, both ICG and ^99m^Tc-nanocolloid are administered. Preoperative preparation at the Nuclear Medicine Department mirrors Phase I, with the exception that skin markings are omitted and surgeons are blinded to lymphoscintigraphy results. Intraoperatively, the SLNB is guided primarily by ICG, with ^99m^Tc-nanocolloid serving as a within-patient control.

ICG is administered as described in the ICG administration section. A caudal axillary incision is made 5–30 min after injection, and SLNB is performed before breast tumour resection. Lymphatic channels may be clipped to prevent ICG leakage. The SLN is defined as the LN with the highest fluorescent signal and is excised first. The axilla is subsequently inspected for residual fluorescent LNs; if present, up to two additional LNs may be excised. All excised LNs are assessed ex vivo for ^99m^Tc uptake. The axilla is then explored for residual ^99m^Tc activity using the gamma probe, supplemented by inspection and palpation. Additional LNs are excised in accordance with the predefined limit of two.

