Acceptability	Extent to which healthcare providers perceive ICG fluorescence to be agreeable, palatable or satisfactory	Perceived relative advantage Ease of use, complexity and patient-friendliness Overall level of acceptability Preference for ICG vs ^99m^Tc-nanocolloid and underlying reason Willingness for sustained use Likelihood of recommending ICG fluorescence to colleagues	Healthcare provider questionnaire (REDCap) with embedded open-text fields (Phase III)

Intervention outcomes	Definition	Outcome measure	Data source/instrument
Effectiveness		Lymph node yield per SLNB procedure (total number of excised lymph nodes, including SLNs and non-SLNs) (all phases) Per-case SLN detection rate, defined as the proportion of SLNB procedures in which ≥1 SLN is identified by the assigned tracer (Phases I and III) Within-patient per-case SLN detection comparing ICG and ^99m^Tc-nanocolloid (Phase II) Per-node SLN detection by tracer, reported separately for ICG and ^99m^Tc-nanocolloid (all phases) Tracer concordance of SLNs (Phase II) Detection time, defined as time from axillary skin incision to excision of the first SLN (all phases) Total SLNB duration, defined as time from axillary skin incision to axillary wound closure (all phases) Pathological classification of excised SLNs (benign, isolated tumour cells, micrometastases, macrometastases), reported per node and per patient and stratified by tracer and study phase (all phases)	Quantitative: perioperative data collected by healthcare providers during SLNB and supplemented with patient file data, entered into REDCap case report forms
Safety		(Serious) adverse events potentially related to ICG administration (Phases II and III)	Quantitative: postoperative REDCap case report forms using patient file data
Costs		Cost overview analysis (healthcare provider perspective): comparison of per-patient and in-hospital costs of SLNBs using ICG vs ^99m^Tc-nanocolloid Budget impact analysis (national scale-up): projected economic impact on the Dutch healthcare system over a 5-year period through phased implementation of ICG-guided SLNB Patient-incurred costs related to SLNB, including travel, sick leave and childcare needs (Phases I and III)	Quantitative: hospital administrative data, financial data and national costing guidelines; ZonMw Budget Impact Analysis tool with sensitivity analysis; phase-specific postoperative patient questionnaire (REDCap)

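### Per-node outcomes enter the Phase I versus III comparison, but the only categorical tests named assume independent observations and nothing accounts for several nodes from one patient

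*Protocol article*

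**What the plan says.** The section Quantitative analysis sets out the between-group methods in one general sentence. It begins "Where applicable, comparisons will be performed using the Student’s t-test for normally distributed continuous variables", gives the Mann-Whitney U-test for non-normal variables, and ends with chi-square or "Fisher’s exact test for categorical variables". Later in that section the significance rule is "All statistical tests will be two-sided, and a p-value of <0.05 will be considered statistically significant".

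The same section states: "A pre–post implementation analysis will compare observational cohorts of Phase I" and Phase III. The outcomes listed for these phases, with 95% CIs, include per-node SLN detection by tracer and the pathology of excised SLNs. Table 1 (Outcomes and outcome measures) has pathology "reported per node and per patient and stratified by tracer and study phase".

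Phase II is analysed separately, within patients. There, "tracer concordance will be evaluated by quantifying agreement at the LN level". Phase II results are descriptive with 95% CIs, and paired methods are used where they fit.

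On the number of nodes, the section Phase II (transition period) says that after the SLN is removed, "up to two additional LNs may be excised" if residual fluorescent nodes are present. Phase III follows the same technique. The Phase I section states no cap and counts two nodes as SLNs when their counts tie.

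**The concern.** Nodes from one patient share the injection, the surgeon, the anatomy and the disease status. Positive correlation within a patient is therefore the natural working assumption, above all for pathology. Chi-square and Fisher tests applied to a table of nodes ignore this, as does a simple binomial interval with the number of nodes as its denominator.

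Per-node detection and pathology class are categorical, so these are the only tests on the list that a reader could apply to them between phases. The mention of paired methods does not close the gap. It concerns Phase II only. It also handles two tracers observed on the same unit, which is a different matter from several units in the same patient.

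At stake is the precision claimed for secondary node-level results. These sit among the real-world effectiveness data that the trial hopes will inform the national guideline.

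**Working it through.** **1. The article's own precision figures.** The section Sample size expects about 280 Phase III procedures. The binomial half-width is 1.96 × √(p(1 − p)/n).
- p = 0.50: 1.96 × √(0.25/280) = 5.86 points (stated: about ±6).
- p = 0.95: 1.96 × √(0.0475/280) = 2.55 points (stated: about ±2–3).

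Both figures reproduce. They count one observation per procedure, so nodes within patients do not affect them. The article states no precision for any per-node outcome.

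**2. Inputs for the per-node case.**
- From the article: up to three excised nodes per patient in Phases II and III (the SLN plus two), and a two-sided 5% level.
- Assumed, because the article gives neither: the distribution of nodes per patient and the within-patient intraclass correlation (ICC).
- Also assumed: the number of nodes is unrelated to the outcome, and both phases have the same design effect.

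**3. Formulas.** With m nodes per patient:
- design effect DE = 1 + (E[m²]/E[m] − 1) × ICC;
- shortfall in CI length = 1 − 1/√DE;
- true error of a nominal 5% test = 2 × (1 − Φ(1.96/√DE)).

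The E[m²]/E[m] form is used because node counts vary between patients. The simpler 1 + (mean − 1) × ICC assumes equal counts and gives smaller values.

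**4. Lower case.** One, two or three nodes in 60%, 25% and 15% of patients.
- E[m] = 0.60 + 0.50 + 0.45 = 1.55
- E[m²] = 0.60 + 1.00 + 1.35 = 2.95, so E[m²]/E[m] = 1.903
- ICC 0.2: DE = 1 + 0.903 × 0.2 = 1.18 and √DE = 1.087
- CIs 8.0% too short; true error 7.1%

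**5. Upper case.** One, two or three nodes in 40%, 35% and 25% of patients.
- E[m] = 0.40 + 0.70 + 0.75 = 1.85
- E[m²] = 0.40 + 1.40 + 2.25 = 4.05, so E[m²]/E[m] = 2.189
- ICC 0.6: DE = 1 + 1.189 × 0.6 = 1.71 and √DE = 1.309
- CIs 23.6% too short; true error 13.4%

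**6. Nearly one node per patient.** One node in 90% and two in 10%.
- E[m] = 1.1, E[m²] = 0.9 + 0.4 = 1.3, and E[m²]/E[m] = 1.182
- ICC 0.2: DE = 1.036, CIs 1.8% too short, true error 5.4%
- ICC 0.6: DE = 1.109, CIs 5.0% too short, true error 6.3%

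**7. Sign.** With ICC = 0 nothing changes. With a negative ICC the naive interval is slightly too wide. For example, with two nodes in each of 280 patients, a per-node proportion of 95% and ICC −0.1, the naive half-width is 1.81 points and the correct one 1.71.

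The error rates in steps 4 to 6 apply to the Phase I versus III per-node comparison. For the Phase II results only the CI shortfall is relevant.

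**The case against.** The strongest objection is that the article does not commit itself to the faulty analysis. The list of tests is general, opens with a qualifier and is not tied to node counts. No interval method is named for any per-node outcome. The section Sample size says that the aim is description rather than formal hypothesis testing. A variance estimator for secondary CIs is also the kind of detail that an article may leave to a fuller document. This stands as far as intervals go: their method is open, not wrong. It does not remove the point for the between-phase comparison, where the article fixes a list of tests, sets a significance level and includes per-node outcomes that none of the listed tests suits.

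Second, a reader might infer that node-level tracer concordance is to be tested with an independence-based test. The text does not support that. Phase II is descriptive with CIs, under a within-patient approach, so no test error rate applies to it.

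Third, the outcomes carry the SLN label. The SLN is the single node with the strongest signal, or two nodes on a Phase I tie. If the analysis keeps strictly to that definition, there is mostly one node per patient and tracer, and the effect is close to nil. This also stands. Against it, agreement is set at the level of the lymph node and pathology is reported per node separately from per patient, which suggests that more than one node per patient is expected to count.

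Fourth, the correlation is unknown, and a definition based on the strongest signal could even make it negative. The size is therefore shown as a range under stated assumptions.

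**Conclusion.** The point holds in a limited form. For the Phase I versus III comparison the article names only independence-based categorical tests, although the outcomes include per-node detection and per-node pathology and a patient can contribute several nodes. If nodes are treated as independent and correlate positively within patients, per-node CIs in all phases are too short, including those for Phase II concordance, and between-phase per-node p-values are too small.

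The size runs from about 8 to 24% in CI length, and 7 to 13% true error for the between-phase test, under the assumptions in the working. With about 1.1 nodes per patient it falls to roughly 2 to 5% in CI length. It would be wrong to conclude that the planned intervals are certainly too narrow: the article gives no interval method, no node counts and no correlation.

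Penetration, the per-case outcomes and the stated precision figures are not touched by clustering of nodes. This is a minor point on secondary outcomes.

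**What to change.** Add one sentence to the section Quantitative analysis: all per-node estimates, concordance intervals and per-node phase comparisons treat the patient as the cluster, by GEE, cluster-robust variance or a bootstrap that resamples patients. In the same place, restrict the chi-square and Fisher tests to outcomes with one observation per patient.

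The cost is small. No new data are needed provided that each node record carries its patient identifier, and R, which the article already names, can do the analysis. Where correlation is positive, the per-node intervals become somewhat wider.
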